## Abstract

**Introduction:**

Sentinel lymph node biopsy (SLNB) is the standard procedure for axillary staging in clinically node-negative breast cancer. Traditionally, SLNB is performed using technetium-labelled (^99m^Tc) nanocolloid, with or without blue dye. However, both tracers have important limitations. Blue dye poses safety risks, while ^99m^Tc-nanocolloid introduces additional hospital visits, radiation exposure, logistical complexity and high costs. Indocyanine green (ICG) fluorescence is a non-radioactive alternative, offering real-time visualisation while addressing many limitations of traditional tracers. Yet, adoption of ICG-guided SLNB remains limited. This trial aims to guide the implementation of ICG-guided SLNB via axillary incision, evaluate its real-world effectiveness and inform conditions for nationwide scale-up.

**Methods and analysis:**

The INFINITE trial is a multicentre, hybrid effectiveness-implementation study employing a stepped-wedge cluster design across seven Dutch hospitals. Clusters sequentially transition from SLNB using ^99m^Tc-nanocolloid alone (Phase I) to ICG as the primary tracer and ^99m^Tc-nanocolloid as a within-patient control (Phase II), and finally to ICG alone (Phase III). The hybrid design enables evaluation of implementation outcomes (penetration, adoption, fidelity, appropriateness, feasibility, acceptability), intervention outcomes (effectiveness, safety, costs) and patient-reported experience (patient satisfaction). The primary outcome is penetration, the proportion of Phase III SLNB procedures performed with ICG alone. An integrated implementation approach combines the Grol and Wensing model (process model), the Consolidated Framework for Implementation Research (determinant framework) and Proctor’s outcomes framework (evaluation framework). Outcomes are assessed quantitatively, supplemented by an embedded mixed-methods component to explain variation in implementation across centres.

**Ethics and dissemination:**

Ethical approval was obtained from the Medical Research Ethics Committees United (6 November 2024; NL87551.100.24). Results will be submitted to open-access, peer-reviewed journals and presented at conferences focused on oncological or image-guided surgery. Implementation tools, including a clinical protocol, implementation guide, educational materials and patient information, will be developed to support national adoption.

**Trial registration number:**

NCT07146295.

STRENGTHS AND LIMITATIONS OF THIS STUDYThe hybrid effectiveness-implementation design enables simultaneous evaluation of implementation outcomes (penetration, adoption, fidelity, appropriateness, feasibility and acceptability), intervention outcomes (effectiveness, safety and costs) and patient-reported experience (patient satisfaction).The stepped-wedge cluster design supports iterative evaluation and progressive optimisation of implementation strategies across diverse hospital settings.Implementation tools, including a clinical protocol, an implementation guide, educational materials and patient information, will be developed, tested and refined during the trial to support national scale-up of indocyanine green-guided sentinel lymph node biopsy.Cluster transitions are based on site readiness rather than random allocation, which may reduce control over potential time-related confounding when comparing the pre-implementation (Phase I) and post-implementation (Phase III) cohorts.Questionnaire-based implementation outcomes (appropriateness, feasibility and acceptability) are assessed at a single time point in Phase III, which may limit characterisation of how these outcomes evolve during implementation.

## Introduction

 Sentinel lymph node biopsy (SLNB) is the standard axillary staging procedure for patients with clinically node-negative breast cancer, guiding both prognosis and adjuvant treatment decisions.^1^,^4^ The current gold standard approach is a radio-guided surgery using technetium-labelled (^99m^Tc) nanocolloid. This technique requires preoperative injection and lymphoscintigraphy to localise the sentinel lymph node (SLN), followed by intraoperative detection with a gamma probe.^5^ To enable visualisation, ^99m^Tc-nanocolloid may be combined with blue dye.^6 7^ This dual-tracer approach is endorsed in the Dutch National Guidelines due to its association with lower false-negative rates.^8^

Despite their diagnostic performance, both traditional tracers have important limitations. ^99m^Tc-nanocolloid exposes patients and staff to ionising radiation, requires coordination with nuclear medicine services and necessitates at least one additional preoperative hospital visit, often at a different facility due to limited availability. Its short half-life restricts surgical planning, and, as a radioisotope, it incurs high costs. The radioactive signal can interfere with tumour markers, and production raises environmental and ethical concerns related to uranium mining.^9^,^13^ Blue dye carries a risk of severe allergic reactions and permanent skin discolouration.^14 15^ The limited added diagnostic value of combining ^99m^Tc-nanocolloid with blue dye often does not justify the increased burden, leading to the common practice of using ^99m^Tc-nanocolloid alone.^16^,^18^ Collectively, these drawbacks highlight the need for alternative techniques.

Fluorescence imaging using indocyanine green (ICG) has emerged as a safe and effective alternative that addresses many limitations of traditional tracers.^19^ ICG is injected intraoperatively after induction of general anaesthesia and enables real-time visualisation of lymphatic drainage using near-infrared fluorescence (NIRF) imaging.^20 21^ The INFLUENCE trial, a previous non-inferiority study, demonstrated that ICG-guided SLNB via axillary incision provided higher SLN detection rates than ^99m^Tc-nanocolloid, with equivalent pathological SLN detection.^22^ Its efficacy has been supported by multiple studies and systematic reviews.^2023^,^32^ A recent meta-analysis of 39 studies (4236 procedures) demonstrated that ICG is superior to blue dye and non-inferior or potentially superior to ^99m^Tc-nanocolloid alone or in combination with blue dye. These results were consistent across per-case and per-node detection rates, sensitivity for metastatic nodes and the number of nodes retrieved.^33^

Beyond diagnostic performance, ICG offers additional advantages to patients, healthcare providers and society. It eliminates preoperative hospital visits and the need for injections while the patient is awake.^23^ As a fluorescent dye, ICG does not depend on specialised nuclear medicine facilities, simplifying logistics and surgical planning. Unlike ^99m^Tc-nanocolloid, ICG does not interfere with tumour markers and provides real-time visual feedback, which may reduce procedure time. Compared with blue dye, ICG has a favourable safety profile and is not associated with permanent skin staining.^26 34 35^ Additionally, ICG-guided SLNB has been associated with lower procedural costs and may contribute to more sustainable and resource-efficient healthcare practice.^36 37^

Despite the growing body of evidence and clear advantages, nationwide uptake of ICG-guided SLNB remains limited and most hospitals continue to rely on ^99m^Tc-nanocolloid. For many years, SLNB has been embedded in a radio-guided workflow using a handheld gamma probe. Transitioning to ICG-guided SLNB replaces this long-standing technique with a camera-based system. This requires hospitals to obtain NIRF imaging equipment, adapt established operative workflows and train surgical teams. Although favourable results with ICG have been reported in the literature, surgical techniques depend on operator skill and confidence and are therefore less readily adopted than pharmacological interventions.^38^,^40^ The transition to ICG may be accompanied by a technical learning curve, underscoring the need to manage early adoption in a manner that preserves oncological safety. Structured implementation support is essential to ensure patients benefit equitably and to mitigate unwarranted practice variation. The INFINITE trial therefore aims to implement ICG-guided SLNB via axillary incision, evaluate its real-world effectiveness and inform the conditions for nationwide scale-up.

## Methods and analysis

### Aims

The primary aim of the INFINITE trial is to implement ICG-guided SLNB via axillary incision into routine clinical practice. Secondary aims are to identify key barriers and facilitators to implementation and to generate evidence to inform conditions for nationwide adoption and future consideration for inclusion in the Dutch national breast cancer guidelines.

### Study design and setting

#### Study design

The INFINITE trial is a multicentre, hybrid effectiveness-implementation study employing a stepped-wedge cluster design.^41^ The hybrid design enables concurrent evaluation of implementation outcomes, intervention outcomes and patient-reported experience, while the stepped-wedge design facilitates phased adoption of ICG-guided SLNB across participating hospitals. Quantitative analyses are complemented by an embedded mixed-methods component to capture contextual and process-related factors relevant to implementation.

Clusters implement ICG-guided SLNB across three sequential phases (figure 1). Phase I (pre-implementation period) is an observational cohort study reflecting current practice in which SLNB is performed using ^99m^Tc-nanocolloid as per standard of care. Phase II (transition period) is a fixed 6-month period in which SLNB is guided primarily by ICG, with concurrent use of ^99m^Tc-nanocolloid as a within-patient control to support a safe transition. Phase III (post-implementation period) is an observational cohort study representing the new practice, with SLNB performed using ICG as a single tracer.

**Figure 1 F1:**
[figure not shown]
INFINITE stepped-wedge cluster trial. Clusters: cluster 1 (Diakonessenhuis, Ziekenhuisgroep Twente), cluster 2 (Dijklander Ziekenhuis, Noordwest Ziekenhuisgroep, Alrijne) and cluster 3 (Canisius Wilhelmina Ziekenhuis, Spaarne Gasthuis). ICG, indocyanine green; ^99m^Tc, radioisotope technetium-99m.

The stepped-wedge cluster design allows for iterative evaluation at each transition. Process evaluations conducted at these intervals will inform adaptation and optimisation of the implementation approach (see an integrated implementation approach). This strategy aligns with the Idea, Development, Exploration, Assessment, Long-term study (IDEAL) framework for surgical innovation, which recognises that surgical innovations often require context-specific refinement during adoption.^38^,^40^

#### Participating hospitals

Seven Dutch hospitals were purposively selected to represent a range of geographic regions, institutional types (eg, OncoMid, Santeon) and organisational scales. This selection captures diversity in implementation context and enhances the relevance of findings for national scale-up (figure 2).

**Figure 2 F2:**
[figure not shown]
Participating and initiating hospitals.

#### Timeline and cluster transition

All participating hospitals commenced Phase I on 18 April 2025. The trial spans 18 months and is divided into six consecutive 3-month periods. Three clusters, each comprising two or three hospitals, transition sequentially from Phase I to Phase II at 3-month intervals.

Cluster transitions are not randomised but scheduled pragmatically based on site readiness, defined as the availability of ICG, access to a NIRF imaging system and completion of training. Although non-randomised transitions may reduce control over potential time-related confounding, the relatively short study duration and stable clinical context minimise the likelihood of major secular trends, making this approach appropriate for a pragmatic implementation study.

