### Statistical analysis

#### Quantitative analysis

Baseline characteristics and quantitative outcome variables will be summarised using descriptive statistics. Continuous variables will be reported as means with SD or as median with IQR, based on distribution. Distributional assumptions will be assessed by visual inspection of histograms, and homogeneity of variances will be evaluated using Levene’s test. Dichotomous and categorical data will be presented as frequencies with percentages.

Where applicable, comparisons will be performed using the Student’s t-test for normally distributed continuous variables, the Mann-Whitney U-test for non-normally distributed continuous variables, and the χ^2^ or Fisher’s exact test for categorical variables.

Penetration, the primary implementation outcome, will be reported as a proportion with corresponding 95% CIs, without formal between-group comparisons. Adoption and fidelity outcomes will be reported descriptively as proportions with accompanying counts. Safety outcomes will be reported descriptively as proportions of patients experiencing ICG-related (serious) adverse events, with corresponding 95% CIs.

Effectiveness outcomes will be analysed according to study phase. A pre–post implementation analysis will compare observational cohorts of Phase I (^99m^Tc-nanocolloid) and Phase III (ICG). For these phases, effectiveness outcomes will be reported with 95% CIs and include per-case SLN detection rates, per-node SLN detection by tracer, number of excised LNs per procedure, detection time, SLNB duration and pathological outcomes of excised SLNs. Phase II will be analysed separately using a within-patient approach. In this phase, per-node SLN detection will be reported separately for ICG and ^99m^Tc-nanocolloid, and tracer concordance will be evaluated by quantifying agreement at the LN level. In addition, a paired within-patient comparison of per-case SLN identification by ICG versus ^99m^Tc-nanocolloid will be performed. Phase II outcomes will be reported descriptively with corresponding 95% CIs, using paired statistical methods where appropriate.

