Several limitations should be acknowledged. Cluster transitions are based on site readiness rather than random allocation. Although reflecting real-world implementation, a non-randomised comparison between pre- and post-implementation phases may be influenced by temporal trends or learning effects within the study period. Yet, the relatively short trial duration and stable clinical context limit the likelihood that such trends materially affect this comparison. The questionnaire-based implementation outcomes (appropriateness, feasibility and acceptability) are formally assessed at a single time point in Phase III. This timing was chosen so that providers can accumulate sufficient experience to give an informed appraisal, but it may limit characterisation of how these outcomes evolve during implementation. Some implementation outcomes, such as fidelity, rely on surgeon self-reporting and may be subject to reporting bias. The sample size is determined by feasibility rather than formal power calculations, which may limit precision for selected secondary outcomes. Although the study includes in-hospital data and collects patient-incurred costs, it is not designed to provide a full societal cost-effectiveness analysis.

Finally, the trial is also conducted in an evolving axillary management landscape, in which recent and ongoing trials suggest that axillary de-escalation, including omission of SLNB, may be safe in selected patients.^64^,^67^ However, this evidence base remains limited, and uptake in routine practice is cautious. SLNB remains indicated for many patients, underscoring the continued need for safe, efficient and consistently implemented techniques.

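### Phases I and III share no calendar period, so the planned pre-post effectiveness comparison is an uncontrolled before-after comparison, which the article describes only as one with reduced time control

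*Protocol article*

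**What the plan says.** The schedule is in Study design and in Timeline and cluster transition. All seven hospitals begin Phase I on the same date, and the 18-month study is cut into six quarters. The rollout is staggered: "Three clusters, each comprising two or three hospitals, transition sequentially from Phase I to Phase II at 3-month intervals". As for its length, Phase II "is a fixed 6-month period in which SLNB is guided primarily by ICG".

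Under Quantitative analysis, the effectiveness outcomes are compared between the Phase I and Phase III cohorts, with two-sample tests named where applicable. The middle phase is kept apart: "Phase II will be analysed separately using a within-patient approach".

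On time trends, the strengths and limitations box after the abstract says that transitions follow site readiness, "which may reduce control over potential time-related confounding when comparing the pre-implementation (Phase I) and post-implementation (Phase III) cohorts". Timeline and cluster transition repeats this and answers that "the relatively short study duration and stable clinical context minimise the likelihood of major secular trends". Strengths and limitations in the Discussion admits that temporal trends or learning may influence the comparison, gives the same reassurance, and then notes that "the trial is also conducted in an evolving axillary management landscape".

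**The concern.** A stepped wedge separates treatment from calendar time only if some clusters are in the new condition while others are still in the old one. The article places the weakness in the non-random order of transition and calls control reduced. A reader would take this to mean that partial control remains and that random order would have given more.

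If the two compared phases never coexist, any drift in case mix, staffing, pathology practice or referral is fully mixed with the change of tracer. This applies to every Phase I versus Phase III outcome: per-case and per-node detection, node yield, detection time, procedure duration and pathology. The trial's secondary aims include informing future consideration for the national guideline, so how much weight this comparison can bear matters.

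**Working it through.** **Inputs.** Common Phase I start; 18 months in six 3-month periods; three clusters moving at 3-month steps; Phase II fixed at 6 months; clusters of 2, 3 and 2 hospitals (Figure 1 caption); about 850 patients in total and about 280 procedures in Phase III (Sample size).

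**Schedule.** Figure 1 is not shown, so I rebuilt the schedule with the first transition at month 3:

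| Cluster | P1 | P2 | P3 | P4 | P5 | P6 |
|---|---|---|---|---|---|---|
| 1 (2 hospitals) | I | II | II | III | III | III |
| 2 (3 hospitals) | I | I | II | II | III | III |
| 3 (2 hospitals) | I | I | I | II | II | III |

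**Check against the article's figures.** Phase III fills 2×3 + 3×2 + 2×1 = 14 of 7×6 = 42 hospital-periods. 850 × 14/42 = 283, against about 280 stated. With n = 280, 1.96 × √(0.50×0.50/280) = 5.9 points and 1.96 × √(0.95×0.05/280) = 2.6 points, matching the stated ±6 and ±2–3. The rebuilt schedule agrees with the article.

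**Overlap.** Let the first transition be at month t. The last cluster leaves Phase I at t + 2×3 = t + 6. The first cluster enters Phase III at t + 6. These are the same date for any t; with t = 3 it is month 9. Phase I lies wholly in P1–P3 and Phase III wholly in P4–P6. Nothing here depends on which hospital is in which cluster, so random order would give the same result.

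**Estimability, Phases I and III only.** A model with seven hospital effects, five period effects and one phase effect has 13 columns. Its rank is 12, and it stays 12 when the phase column is removed. The phase column equals the sum of the P4, P5 and P6 indicators, so the effect is not estimable. A linear trend in place of free period effects would make it estimable, but only by extrapolation.

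**Distance in time.** Using period midpoints weighted by hospitals:

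- Phase I: (7×1.5 + 5×4.5 + 2×7.5)/14 = 48/14 = 3.4 months.
- Phase III: (2×10.5 + 5×13.5 + 7×16.5)/14 = 204/14 = 14.6 months.
- Gap: 156/14 = 11.1 months.

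The documents give no size for any trend. As an assumed range, drifts of 0.1, 0.2 and 0.3 points per month would produce differences of 1.1, 2.2 and 3.3 points with no tracer effect.

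**With Phase II included.** Hospital, period and three-level phase effects give 14 columns and rank 14 (13 without the Phase III term), so III minus I is estimable. The link is indirect: Phase I meets Phase II in P2–P3, and Phase II meets Phase III in P4–P5. Variances, in units of one cell's variance (equal cells, independent errors):

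- Unadjusted III minus I: 1/14 + 1/14 = 0.1429.
- Time-adjusted, three phases: 1.3125.
- SE ratio: √(1.3125/0.1429) = 3.03.

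With 850/42 = 20.2 patients per cell, the 95% half-width for a continuous outcome goes from 1.96 × √(0.1429/20.2) = 0.16 SD to 1.96 × √(1.3125/20.2) = 0.50 SD.

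**The case against.** The article discloses much of this. It calls the analysis pre-post, describes the cohorts as observational, and says temporal trends or learning may influence the comparison. It justifies the stepped wedge mainly by phased rollout, iterative evaluation and safe transition, not by separating time from treatment. Under Sample size it says the aim is to describe rather than to test hypotheses, although tests and a significance level are then named. A sensitivity model could also be left to a fuller plan. These points limit the severity. They do not repair the statement that control is reduced because the order is not random: it is absent under free period effects, and for a different reason. Nor can any later plan recover it from Phases I and III alone without assuming a form for the trend.

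A reader might infer that the article contradicts itself by claiming stability while describing an evolving axillary landscape. The text does not support that. It says omission of SLNB may be safe in selected patients, that the evidence is limited and that uptake is cautious. This is in tension with a stable context but does not refute it, and the document reports no change in who receives SLNB during the trial.

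A reader might also infer that the Phase II paired comparison should become the lead evidence. It is free of calendar-time confounding, but Phase II is the learning period, nodes are sought with ICG first and the gamma probe follows, and it does not show how ICG performs alone.

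Finally, learning that depends on time since transition would not be removed by calendar-period adjustment.

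**Conclusion.** The point holds. On the stated schedule Phases I and III have zero calendar overlap. With Phase II set aside, their comparison is an uncontrolled before-after one, with mean times about 11 months apart when the first transition is at month 3. Its validity rests wholly on there being no secular change, which the article asserts and does not test.

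The non-overlap is exact for the plan as written; an unplanned delay of one cluster could create some. Non-estimability is exact for unrestricted period effects. The SE ratio of about 3.0 assumes equal hospital-period sizes, independent errors and period effects common to all hospitals.

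The scope is the Phase I versus Phase III effectiveness outcomes. Penetration is reported without between-group comparison and is unaffected. The documents do not show that a trend exists or how large it would be.

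**What to change.** 1. In the strengths and limitations box, in Timeline and cluster transition, and in the Discussion limitations, state that Phases I and III do not overlap in calendar time. Say that the comparison is an uncontrolled before-after one that depends wholly on no secular change, and that this follows from the step and transition lengths, not from the non-random order. Soften the claim that major trends are made unlikely.
2. For the effectiveness outcomes measured in all phases (node yield, detection time, SLNB duration, pathology), add a sensitivity model that includes Phase II, with hospital, 3-month period and three-level phase effects. Plot these outcomes by hospital and period.
3. The paired Phase II comparison, already planned, may be cited as supporting evidence free of calendar-time confounding, alongside Phase III and not in its place.

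The cost is a few sentences, one added model and a set of plots. No data collection changes. The downside is that the time-adjusted intervals are about three times as wide and the pre-post claim becomes weaker.
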